### Data collection/Management process

The primary outcome measures were the length of hospital stay and any psychiatric rehospitalization during the 12 months post discharge. The secondary outcome measures included: 1) symptom severity, 2) clinical global impression of the illness, 3) global functioning, 4) quality of life, and 5) patients’ satisfaction with service. We also performed a direct cost-effectiveness analysis.

Data were collected from the intervention and control groups at time of index admission, discharge and at each follow-up point. Follow-up ratings in Iran and Nour hospitals were scheduled 3, 6, and 12 months and in another one (in Roozbeh hospital) at 4, 8 and 12 months following discharge and were performed in the outpatients department or at home by an experienced and trained clinician.

We used the following tools in baseline assessment, when the patients were discharging from the hospital, and the follow-up ratings: the Positive and Negative Symptoms Scale (PANSS) for psychotic symptoms
[57], the Young Mania Rating Scale (YMRS) for manic symptoms
[58], the Hamilton Depression Rating Scale (HDRS) for depressive symptoms
[59], the Clinical Global Impression (CGI) for illness severity
[60], the Global Assessment of Functioning (GAF) for global functioning
[61], the Farsi translation World Health Organization Quality of Life (WHOQOL-BREF) for quality of life
[62] and Client Satisfaction Questionnaire (CSQ-8) for the assessment of patients' satisfaction with the services
[63].

Data with regard to rehospitalizations and length of hospital stay were carefully collected and evaluated during follow-up assessments by a questionnaire which was designed by the research team and asks questions from patients and their relatives; medical records were reviewed as well. It should be mentioned that in the follow-up ratings a Cost Analysis Questionnaire were also used for calculating direct costs for the 12 month follow-up period. Medical costs included costs of hospitalization, outpatient and community visits, family psychoeducation, social skills training, medicine, and complementary-alternative therapies in both groups and also all payments for providing specific healthcare of the interventions. Non-medical costs included costs of transportation of patients, caregivers and healthcare teams (in the intervention group). Raters were clinical psychologists or general practitioners who were trained in a 2-day workshop on how to use data collection tools before the initiation of the study. Inter-rater reliability of ratings was also examined. We chose raters not from care providers to minimize bias.

Studies show that the rate of “loss to follow up” for ratings in these setting is high
[28]. For this reason, patients and their family members were asked to provide their address and phone number at the beginning of the study. One week prior to the follow-up rating appointment, the patient or other named contact were contacted to determine if they would attend their appointment. The day before their appointment, patients were contacted to remind them that their follow-up appointment is due the next day. If the patients were unable to be contacted, or the patients did not show up for their appointment, the follow up team contacted them again. Eventually the research coordinator visited the patients at home and found out if they still stay in that address and also if they want to continue participating in the study. If the patient was no longer living in that address or he/she did not want to participate in the study any longer, he/she was excluded from the study.

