### Sample size calculation

Sample size calculation was based on the length of hospital stay as the primary outcome measure. The following formula was used for the calculation:

$$n=2{\left[z_{\left(1-\alpha /2\right)}+z_{\left(1-\beta \right)}\right]}^{2}\times \left(SD^{2}\right)/d^{2}$$

where d = (delta [difference]). Here delta equals to our estimate of the difference between length of hospital stay in experimental and control groups. In a study on the efficacy of home care service
[64], it was shown that the mean hospitalization days in the home care group was about a third of that in the treatment as usual group (14.5 vs. 41.7 days). Also in an unpublished study ([name], Personal Communication), we found that mean hospital stay of patients with severe mental disorders equals to 45 days with the SD of 18 days. For the present study we aimed for a more conservative and still important difference. We hypothesized that the home care program leads to at least 10 days reduction in hospital stay (×1- × 2 = 10, SD = 18, Cohen's d = 0.6). Sample size was estimated 45 per group; assuming about 30% losses to follow-up, sample size was calculated 60 per group (in total: 120). In one of the centers (Roozbeh hospital) the sample size was 80 per group (in total: 160), because the caseload was higher that allowed recruiting more patients in the same period.

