### Planned analysis

Descriptive summaries of socio-demographic and clinical data will be provided for all subjects at different time points. These include means and standard deviations, or proportions. The clinical ratings will be summarized in terms of the total score, and the proportion of patients improving from baseline. An “intention to treat” approach will be employed. Baseline qualitative variables will be compared between the intervention and control group by chi2 test. The quantitative variables will be compared using *t*-test and Mann–Whitney *U* test. The quantitative primary and secondary outcomes measures will be compared using general linear model (GLM) repeated measure analysis. Length of stay will be assessed in each period of follow-up; we analyze it both as the cumulative hospital stay (using *t* test) and as the stay in each follow-up period. The second analysis will be performed by repeated measures analysis of variance analysis.

We calculate all direct medical and non-medical costs of care from a societal point of view. To do that, total costs of care (not just out-of-pocket payments) were considered. Medical costs included costs of hospitalization, outpatient and community visits, family psychoeducation, social skills training, medicine, and complementary-alternative therapies in both groups and also all payments for providing specific healthcare of the interventions. Non-medical costs included costs of transportation of patients, caregivers and healthcare teams (in the intervention group). We divide incremental direct costs (Costs in the intervention group minus control group) by incremental effects (based on primary and secondary outcomes) to calculate incremental cost-effectiveness ratio (ICER). Statistical package for social sciences (SPSS version 18.0) will be used for data analysis.

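### The exclusion rule and the repeated measures model do not deliver the declared intention-to-treat approach for the rating scales and by-period hospital stay, with about 30% loss expected

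*Protocol article*

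**What the plan says.** - **Analysis principle.** Planned analysis states: "An “intention to treat” approach will be employed". The article does not define the set.
- **Exclusion after randomisation.** Data collection/Management process describes reminders, repeat contact and finally a home visit for patients who miss a rating. It then gives two triggers. One is a change of address: "If the patient was no longer living in that address". The other is unwillingness to continue, and the sentence ends with the consequence for both: "he/she did not want to participate in the study any longer, he/she was excluded from the study".
- **Model.** Planned analysis states: "The quantitative primary and secondary outcomes measures will be compared using general linear model (GLM) repeated measure analysis". On length of stay it adds "we analyze it both as the cumulative hospital stay", by t test, and as the stay in each follow-up period. For the by-period analysis: "The second analysis will be performed by repeated measures analysis of variance analysis". The software is fixed too: "Statistical package for social sciences (SPSS version 18.0) will be used for data analysis". No test is named for any rehospitalisation, the other primary outcome.
- **Expected loss.** Sample size calculation goes from 45 to 60 per group "assuming about 30% losses to follow-up". One centre recruits 80 per group.
- **Source of hospitalisation data.** Data collection/Management process describes a questionnaire put to patients and relatives at the follow-up assessments, with medical records also reviewed. It does not say whether that review goes on after a patient is excluded.

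**The concern.** Intention to treat means analysing every randomised patient in the arm to which he or she was allocated. Two stated elements pull against this. First, patients are excluded after randomisation for reasons that include a change of address, which is not a withdrawal of consent. Second, the repeated measures procedure works on complete rows: one missing rating removes the patient, including the ratings that were obtained.

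This matters here because substantial loss is expected and because the intervention works through contact (home visits and telephone prompts). Loss could therefore differ by arm and be related to relapse. The enlarged sample protects power, and does nothing against selective loss.

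**Working it through.** **1. The plan's own sample size.** Alpha and power are not stated; I assume two-sided 0.05 and 80%. The article's formula is n = 2(z₁₋α/₂ + z₁₋β)² × SD²/d².
- With the stated effect size of 0.6: 43.6, so 44 per group by the normal approximation and 45 by the t distribution. The stated 45 reproduces.
- With the unrounded 10/18 = 0.556: 50.9, so 51. The 45 therefore rests on rounding up.
- Inflation: 45 × 1.3 = 58.5, close to the stated 60. Dividing instead gives 45/0.70 = 64.3, so 65. Either way, the calculation gives lost patients no weight in the analysis.

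**2. Patients left in a complete-case repeated measures model.**
- At 30% loss: 60 × 0.70 = 42 per group, and 80 × 0.70 = 56 at the larger centre.
- Each patient has three follow-up ratings. If 10% or 15% missed each one independently (an assumption), the complete share would be 0.90³ = 73% or 0.85³ = 61%.

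**3. Which outcomes the listwise mechanism reaches.**

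| Outcome | Stated method | Listwise deletion? | Exposed to the exclusion wording? |
|---|---|---|---|
| Rating scales | GLM repeated measures | Yes | Yes |
| Stay by period | Repeated measures ANOVA | Yes | Yes |
| Cumulative stay | t test | No | Yes, if removed from the analysis set or no 12-month total |
| Any rehospitalisation | None named | No | Yes, on the same condition |

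That the procedure drops incomplete rows is a property of the method. The article does not state it.

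**4. Power, if excluded patients also leave the cumulative-stay comparison** (normal approximation, 42 instead of 60 per group):
- effect size 10/18: 86% falls to 72%;
- effect size 0.6: 91% falls to 79%.

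**5. Bias: illustration only.** None of these inputs is in the article. Assume no true effect, 50% readmission in both arms and 65% among the lost. The completers' rate is (0.50 − loss × 0.65)/(1 − loss).
- Loss 40% TAU, 20% aftercare: 0.24/0.60 = 40.0% against 0.37/0.80 = 46.25%. Aftercare looks 6.25 points worse.
- Loss 35% and 25%: 0.2725/0.65 = 41.9% against 0.3375/0.75 = 45.0%. Aftercare looks 3.1 points worse.
- Loss 30% in both arms: 0.305/0.70 = 43.6% in each. No bias.

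In days: if the lost would have had g more hospital days than completers in both arms, the between-arm difference shifts by (loss in TAU − loss in aftercare) × g. For g = 5 to 15 and loss of 40% against 20%, that is 0.20 × g = 1 to 3 days against the 10-day target. With equal loss and equal g it is zero.

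**The case against.** The exclusion sentence closes a paragraph about tracing patients for ratings. It can fairly be read as saying that ratings stop, not that the patient leaves the analysis. Planned analysis also promises descriptive summaries for all subjects at the different time points. Imputation is not mentioned, but it is not ruled out, and missing-data rules commonly sit in an analysis plan that is not shown here. Follow-up was also protected: raters were not care providers, the tracing steps are described without distinction by arm, ratings could be done at home, and patients had to live with a family member.

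Much of this stands, and it rules out several stronger readings that a reader might infer:

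- *The whole trial is a completers analysis.* Listwise deletion does not touch the t test on cumulative stay or the rehospitalisation outcome.
- *Data already collected are thrown away by the exclusion rule.* The text does not say this. For the rating scales and by-period stay it follows from the named model, not from the rule.
- *The primary outcome is independent of attendance.* It relies partly on a questionnaire at assessments, and records may miss admissions elsewhere after a move.
- *Loss will differ by arm and favour the intervention.* Differential loss is plausible but nowhere quantified, and in the illustration the bias runs against aftercare.

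What does not stand is that the point is only missing detail. The exclusion wording and the model are both stated, and an unseen plan would have to override them to restore intention to treat.

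**Conclusion.** The point holds in limited form. For the rating scales and by-period stay, the named model turns the declared intention-to-treat approach into a completers analysis on about 42 of 60 patients per group. This takes the article's own planning figure of about 30% as the share with an incomplete record, and the default handling of missing visits. For cumulative stay and any rehospitalisation the defect is conditional: it arises if exclusion means removal from the analysis set, and the article does not settle that.

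Neither the size nor the direction of bias can be derived from the document. The 6-point figure depends entirely on assumed loss and readmission rates. Under those rates it would hide a benefit of aftercare rather than create one, and it vanishes when loss and the prognosis of the lost are equal across arms.

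**What to change.** 1. **Exclusion wording.** State that moving or stopping participation ends ratings only. All randomised patients stay in the analysis set as allocated, with the data collected up to that point.
2. **Hospitalisation data.** Where consent allows, continue the medical-record review for admissions to month 12. Admissions to other hospitals after a move may be missed, so treat such patients as having partial follow-up up to the last date on which their admission status is known. Do not enter them as having zero days or no readmission.
3. **Model.** Replace GLM repeated measures and repeated measures ANOVA with a likelihood-based linear mixed model (SPSS MIXED) using all available visits. It rests on data being missing at random, a weaker assumption than complete-case analysis needs.
4. **Hospital days with partial follow-up.** Use a count model, for example negative binomial with log days at risk as offset, in place of the t test on an incomplete total.

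**Cost.** The model change is a different procedure in the same software, and the article still describes the analysis in the future tense. The record check is modest extra work, but it is more than rewording: follow-up is reported in the past tense, so it would partly be retrospective and must respect the right to withdraw. Some under-capture of admissions outside the trial hospitals would remain and should be reported.

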### Blinding

The nature of such services prevents adequate blinding of participants. It was not possible to blind the raters who will perform follow-up evaluations on cases and controls because he has a direct contact with patients when rating patients.

### Quality assurance

A single team trained all the care providers and raters in different sites with a single training module. A single guideline was used by all care providers. There were supervisors for each center who oversaw the whole process of the study. They used the same protocol for supervision that consisted of weekly meetings, checking the data collection procedures, supervision of training sessions, etc. The same supervision procedure was employed for the whole process of case recruitment and data collection.

### Sample size calculation

Sample size calculation was based on the length of hospital stay as the primary outcome measure. The following formula was used for the calculation:

$$n=2{\left[z_{\left(1-\alpha /2\right)}+z_{\left(1-\beta \right)}\right]}^{2}\times \left(SD^{2}\right)/d^{2}$$

where d = (delta [difference]). Here delta equals to our estimate of the difference between length of hospital stay in experimental and control groups. In a study on the efficacy of home care service
[64], it was shown that the mean hospitalization days in the home care group was about a third of that in the treatment as usual group (14.5 vs. 41.7 days). Also in an unpublished study ([name], Personal Communication), we found that mean hospital stay of patients with severe mental disorders equals to 45 days with the SD of 18 days. For the present study we aimed for a more conservative and still important difference. We hypothesized that the home care program leads to at least 10 days reduction in hospital stay (×1- × 2 = 10, SD = 18, Cohen's d = 0.6). Sample size was estimated 45 per group; assuming about 30% losses to follow-up, sample size was calculated 60 per group (in total: 120). In one of the centers (Roozbeh hospital) the sample size was 80 per group (in total: 160), because the caseload was higher that allowed recruiting more patients in the same period.

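### The planning SD of 18 days is not shown to fit the primary outcome of 12-month cumulative hospital days, which includes zeros; at 60 recruited per group the power is probably overstated

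*Protocol article*

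**What the plan says.** Under Sample size calculation, the Protocol article takes its variability from an unpublished study: "mean hospital stay of patients with severe mental disorders equals to 45 days with the SD of 18 days". It does not say whether this describes one admission or the total over a period. Just before, it cites a home-care study with 14.5 against 41.7 hospital days, without an SD. The planning effect is then set: "We hypothesized that the home care program leads to at least 10 days reduction in hospital stay", with "SD = 18, Cohen's d = 0.6". The result is "Sample size was estimated 45 per group", raised to 60 for about 30% loss, with 80 per group at one of the three hospitals because of its larger caseload.

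Under Data collection/Management process, the outcome has a fixed window: "The primary outcome measures were the length of hospital stay and any psychiatric rehospitalization during the 12 months post discharge". Under Planned analysis, length of stay is treated in two ways: "we analyze it both as the cumulative hospital stay", by t test, and as days in each follow-up period, by repeated measures. The analysis is to follow intention to treat. No section gives an expected readmission rate, a number of readmissions per patient, or an SD of 12-month days.

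**The concern.** Under intention to treat, a patient who stays out of hospital for the year counts as zero days. Cumulative days therefore mix a group at zero with a group of readmitted patients, and the gap between the two adds variance that the spread of stay lengths does not contain. The sample size formula is proportional to the square of the SD, so a moderate understatement has a large effect.

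At stake is how a null result would be read. The article says the findings may influence national policy and programme planning. If the comparison has roughly even odds of detecting a true 10-day benefit, a non-significant difference is weak evidence against the service, yet the stated calculation would make it look informative.

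**Working it through.** **Inputs.** From Sample size calculation: difference 10 days, SD 18, mean 45, 45 evaluable and 60 recruited per group, about 30% loss. Alpha and power are not stated. I assume two-sided 5% (the formula uses the 1 − α/2 quantile) and 80%. The share readmitted, p, is not in the document, so I vary it from 30% to 90%.

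**1. The plan's own figure.** n = 2(1.96 + 0.84)² SD²/d² = 15.70 × SD²/d².
- With the rounded d = 0.6: 15.70/0.36 = 43.6, so 44 (45 by the t-test formula). The stated 45 reproduces.
- With the unrounded 10/18 = 0.556: 15.70 × 324/100 = 50.9, so 51.
- 60 less 30% leaves 42, and power for 10 days at SD 18 is then 72%.

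So part of the shortfall comes from rounding and loss, before the SD is questioned. The fair comparators below are 51 and 72%.

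**2. Reading A: 45 and 18 are 12-month totals including zeros.** For any non-negative variable with mean m and a share p above zero, SD ≥ m√(1/p − 1), hence p ≥ 1/(1 + (SD/m)²).
- m = 45: p ≥ 1/(1 + 0.16) = 0.862.
- m = 35 (after a 10-day reduction, same SD): p ≥ 1/(1 + 0.2645) = 0.791.

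This holds whatever the distribution.

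**3. Reading B: 45 and 18 describe one stay.** Assume one such stay per readmitted patient. Including zeros, SD² = p·18² + p(1 − p)·45². If the 10 days come only from fewer readmissions, the aftercare share is p − 10/45 = p − 0.222. The n uses the average of the two variances.

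Example, p = 0.5:
- Control variance: 162 + 506.25 = 668.25 (SD 25.9).
- Aftercare variance, share 0.278: 90 + 406.25 = 496.25 (SD 22.3).
- Average: 582.25, SD 24.1.
- n = 15.70 × 582.25/100 = 91.4, so 92.

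| Control readmitted | SD control / aftercare | n per group | Power, 42 per group | Power, 98 per group |
|---|---|---|---|---|
| 30% | 22.9 / 13.1 | 55 | 69% | 96% |
| 40% | 24.8 / 18.8 | 77 | 55% | 89% |
| 50% | 25.9 / 22.3 | 92 | 48% | 83% |
| 60% | 26.1 / 24.5 | 101 | 44% | 79% |
| 70% | 25.5 / 25.7 | 103 | 43% | 78% |
| 80% | 24.1 / 26.1 | 100 | 45% | 80% |
| 90% | 21.8 / 25.7 | 90 | 49% | 84% |

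The column for 98 is 140 recruited per group (60 + 80) less 30%. Against 51, the need is 1.1 to 2.0 times as large (55/51 to 103/51).

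Readings A and B use 45 differently, as the overall mean and as the mean of a stay. They are alternatives, and their results must not be added together.

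**4. Power for 10 days by SD alone.**

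| SD | 42 per group | 98 per group |
|---|---|---|
| 22 | 55% | 89% |
| 25 | 45% | 80% |
| 30 | 33% | 65% |
| 35 | 26% | 52% |

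Repeat admissions would push the SD upwards from reading B. The document gives nothing from which to say how far.

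**The case against.** The strongest reply is that the document does not say what the source measured. The 45 days stand next to arm means from a trial, so they may be totals over a period. The Background describes repeated rehospitalisation as common, so a high readmission share is not absurd. This stands: a reader might infer that SD 18 is certainly a per-stay figure, but that is only one reading. Nor does a high share conflict with having any rehospitalisation as a second primary outcome, because no rate is stated for it to contradict.

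The second reply is that this is one trial in three hospitals, and no section plans separate tests by centre. With 140 recruited per group, most scenarios reach or come close to 80% power. If 60 is meant per centre, 60 + 60 + 80 = 200 recruited leaves 140 evaluable, and power is at least 90% throughout the one-stay model. This also stands, so the document does not support the inference that the whole trial is badly underpowered.

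Third, the 10-day effect is worded for home care, while some intervention patients receive telephone prompts. A reader might infer a diluted effect of some definite size. The document gives neither the share in each mode nor an effect for prompts, and 10 days was chosen as conservative against a cited difference of 27.2 (41.7 − 14.5). No figure can be put on dilution.

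What does not fall away is that the printed calculation rests on 45 evaluable per group and SD 18, and neither is tied to the outcome analysed.

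**Conclusion.** The point holds in limited form. SD 18 is not shown to be the SD of 12-month cumulative days. If it is, it carries an unstated requirement that at least 86% of patients are readmitted at mean 45, and 79% at mean 35. If it is not, the zeros are missing. In the one-stay model with 30-90% of controls readmitted, 55-103 evaluable per group are needed, and 42 give 43-69% power against 72% at SD 18.

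These figures rest on an assumed readmission range, one stay per readmitted patient, an effect acting only through fewer readmissions, two-sided 5% and a normal approximation. The shortfall applies to the stated 60 per group. Pooled at 98 evaluable per group the same model gives about 78-96%, so the conclusion for the whole trial depends on a total that the article does not state clearly. The fault lies in the planning figure; the type I error of the t test is not in question.

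**What to change.** 1. State what the unpublished source measured: one admission or total days, over what period, and whether patients with no days were counted.
2. Replace SD 18 by the SD of 12-month cumulative days including zeros, from the centres' records or from blinded pooled trial data.
3. State the total per group over the three hospitals, and restate power for 10 days over a range of SDs, for example 22-35, for the whole intervention arm and after the expected loss. Use the unrounded 10/SD.
4. Adjust the comparison of cumulative days for the severity stratum used in randomisation and for centre, and report the mean difference in days with its confidence interval.

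A count model such as the negative binomial is optional and does not replace the restated SD. The cost is a short data extraction, a revised paragraph and probably a less favourable power figure. No patients are added.

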#### A) Treatment follow-up

The aftercare service consisted of services for two groups of patients: 1) Patients who had severe mental illness with poor compliance that required more assertive follow-up; for example patients with poor medication compliance or those who missed appointments, patients with a very severe and debilitating illness, or patients who were home-bound; this group received home care. Home visits were made once in a month with the exception of the first three months, which were twice per month. Extra visits were made more frequently for unstable patients. In each visit a team of general practitioner and another professional (a social worker or a psychologist) made visits, prescribed medications and provided education and support to patients. 2) Patients with more compliance who needed follow-up but not as assertive as the former group; this group received telephone follow-up prompts to attend the outpatient clinic for the follow-up visits that was usually on a monthly basis. In each outpatient visit a psychiatrist assessed the patients‘clinical status and prescribed medications. Both of these two follow-up modes were different components of the active intervention and the patients inside the intervention group could cross between these two modes of care based on their improvement or deterioration during the study period. All these assignments were made by clinical judgment of supervising psychiatrist of the research team at each center.

Programs for family psychoeducation and social skills training (below) were incorporated into the above-mentioned modes of treatment follow-ups.

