### Trial randomization procedure

After obtaining a written consent, patients were divided randomly into two groups of intervention and control (TAU). There was equal allocation of participants between arms of the study (allocation ratio 1:1). Randomization was provided by an independent statistician at the medical university. Eligible patients were assigned to intervention or control (TAU) groups by stratified balanced block randomization method with allocation concealment. There was a psychiatrist at each center responsible for concealment procedures. After assignment, each patient of Intervention group was classified according to the severity criterion by the research coordinator (see above) and then received the needed mode of care: either home care or telephone prompts for outpatient attendance. Therefore, the latter was not random but based on patients’ needs.

However, to ensure comparability of intervention and control groups with regard to severity of patients’ illnesses we did a stratified randomization procedure. Patients were first categorized according to its severity that included measures for frequent admissions and/or treatment compliance. Then patients in each group of severity (high or low) were randomized into aftercare or treatment-as-usual groups. For example, patients who had an illness with high severity that required home care (in the intervention group) were evenly randomized into two groups.

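### The 10-day reduction behind the sample size is sourced from and worded for home care, but the tested arm mixes home care with telephone follow-up; power may be lower unless 10 days is the whole-arm average

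*Protocol article*

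**What the plan says.** The Protocol article, section Sample size calculation, sizes the trial on one outcome: "Sample size calculation was based on the length of hospital stay as the primary outcome measure". It defines the target difference for the randomised comparison: "Here delta equals to our estimate of the difference between length of hospital stay in experimental and control groups". The evidence offered for its size is a study of home care, where "mean hospitalization days in the home care group was about a third of that in the treatment as usual group (14.5 vs. 41.7 days"). The authors then step down from that figure ("For the present study we aimed for a more conservative and still important difference") and write: "We hypothesized that the home care program leads to at least 10 days reduction in hospital stay". The inputs are a difference of 10 with "SD = 18, Cohen's d = 0.6". The result is 45 per group, raised to 60 per group for about 30% loss. One centre took 80 per group. No overall total, alpha or power is given as a number.

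The sections Intervention group and A) Treatment follow-up describe two modes within the aftercare arm. Patients with poor compliance, very severe illness or who are home-bound receive home visits. For the more compliant patients, "this group received telephone follow-up prompts to attend the outpatient clinic for the follow-up visits". Patients may move between modes on clinical judgement. Sections B and C give family psychoeducation and skills training to both modes, in different formats.

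Under Trial randomization procedure, patients are first classed by severity: "Then patients in each group of severity (high or low) were randomized into aftercare or treatment-as-usual groups". The Planned analysis compares the whole arm with usual care, by a t test on cumulative stay and repeated-measures analysis of variance on stay by period. Severity is not mentioned there.

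**The concern.** The definition of the difference refers to the whole experimental arm. The evidence and the wording of the hypothesis refer to one mode within it. The contrast tested is an average over both modes, weighted by how many patients receive each, and nothing in the article supports 10 days for the telephone mode. For those patients the follow-up contrast is narrower than for home care: they are prompted to attend roughly monthly clinic visits, and the Control group section schedules usual-care patients for a visit at two weeks and then monthly.

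If 10 days describes home care alone, the whole-arm effect could be smaller even when home care performs exactly as assumed. A null overall result would then be hard to interpret. The severity strata, which could show whether the effect differs between the patients each mode was meant for, are used to randomise but not to analyse.

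**Working it through.** **Inputs from the article.** Difference 10 days; SD 18; printed d 0.6; 45 per group before loss and 60 after; about 30% loss; one centre with 80 per group; cited means 14.5 and 41.7 days.

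**Assumptions.** Two-sided alpha 0.05 and 80% power (the formula shows symbols only); the share of the arm on home care, *h*; the telephone-mode effect, *e*. The article gives neither *h* nor *e*, so a range is shown.

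**1. The plan's own figure.** n = 2(z₁₋α/₂ + z₁₋β)² × SD²/d².
- With the printed d = 0.6: 2 × (1.960 + 0.842)² / 0.36 = 43.6, so 44; the exact t test gives 44.6, so 45. This reproduces the stated 45.
- With the unrounded inputs: 10/18 = 0.556, and 2 × (1.960 + 0.842)² × 324/100 = 50.9, so 51.

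**2. Numbers analysed.**
- If 60 per group is the whole trial: 60 × 0.7 = 42 per arm.
- If 60, 60 and 80 per group are centre sizes that are pooled: 200 × 0.7 = 140 per arm.

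**3. Baseline, no dilution.** Exact t-test power for 10 days, SD 18, is 71% at 42 per arm and above 99% at 140. At 42 per arm, power is thus below 80% before any dilution. That comes from rounding 0.556 up to 0.6 and from the loss allowance (45 is inflated to 60, of which 70% is 42). It is a separate matter and should not be counted against the mixed arm.

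**4. If 10 days is the home-care effect only.** Whole-arm effect = *h* × 10 + (1 − *h*) × *e*.

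| *h* | *e* (days) | Whole-arm effect | Power, 42 per arm | Power, 140 per arm | n per group for 80% (plan's formula) |
|---|---|---|---|---|---|
| any | 10 | 10 | 71% | >99% | 51 |
| 0.7 | 5 | 0.7×10 + 0.3×5 = 8.5 | 57% | 98% | 71 |
| 0.5 | 5 | 0.5×10 + 0.5×5 = 7.5 | 47% | about 93% | 91 |
| 0.5 | 0 | 0.5×10 + 0 = 5 | 24% | 64% | 204 |

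With 140 per arm, 80% power holds down to a difference of about 6.0 days.

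**5. If 10 days is already the whole-arm average.** The cited difference is 41.7 − 14.5 = 27.2 days. If that held for home care and the telephone mode had no effect, the arm would average 10 days at *h* = 10/27.2 = 37%. Read this way, there is no loss.

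**The case against.** The strongest reply is that the section's formal definition of the difference is experimental versus control, which is the contrast tested, and that naming home care two sentences later is loose wording. In support, the 27.2-day difference was cut to 10, and step 5 shows that this cut could cover a mixed arm. Diluting the 10 days again may then discount twice. This stands as a possible reading. However, the article calls the 10 days only conservative, never an average over modes, and still attributes it to home care. The text does not settle which reading is meant.

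Three further points stand.
- Telephone-mode patients receive much more than a call: six two-hour multiple-family sessions and ten skills sessions, neither of which usual care provides. A zero telephone-mode effect is therefore a boundary case, not an expectation.
- One centre alone enrolled 160, so 120 is hard to read as the three-centre total. At about 140 analysed per arm, moderate dilution is absorbed. The article does not state the total, so this reassurance cannot be confirmed.
- The objective is the aftercare package, and supportive subgroup models are often left to an analysis plan. The lack of one is not an error here. It is suggested because randomisation within severity already makes it available at little cost.

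A reader might infer that within-stratum differences would give randomised estimates of home care and of telephone follow-up. They would not. Strata are fixed by baseline severity, and patients may cross between modes afterwards.

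**Conclusion.** The point holds as a gap in justification with a conditional effect on power. The article does not support 10 days for the arm it randomises and tests, and its definition and its hypothesis refer to different things.

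If 10 days is the home-care effect only, with half the arm on home care and 5 days for the telephone mode, the loss due to mixing is from 71% to 47% at 42 per arm, or from above 99% to about 93% at 140. If 10 days is the whole-arm average, the loss is nil. All of this rests on SD 18, two-sided 0.05, and an assumed share and telephone-mode effect.

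A reader might go further and conclude that the sample size fails to deliver its intended power. The article does not support that: it prints no power figure, defines the difference for the whole arm, discounts the cited effect heavily, and may have about 140 evaluable patients per arm. This is worth correcting, but it does not show that the trial is underpowered.

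**What to change.** In the sample size section, state the 10 days as the expected average over the whole aftercare arm. Give the assumed home-care share and telephone-mode effect that lead to it, and the resulting power at the actual total size, with a short range as in the table above. State alpha and the overall total alongside. No extra enrolment is needed.

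In the planned analysis, include the pre-randomisation severity stratum in the length-of-stay model. From the same model, with an arm-by-severity term, report the aftercare-minus-usual-care difference in hospital days within each stratum, with confidence intervals, as supportive. Describe these as effects of the aftercare strategy by baseline severity, not as effects of each mode.

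The cost is a reworded paragraph, possibly a less favourable stated power, and one extra model term. The stratum estimates will be imprecise: with two equal strata and SD 18, the 95% half-width is about 1.96 × 18 × √(2/21) = 10.9 days at 42 per arm, and 1.96 × 18 × √(2/70) = 6.0 days at 140 per arm.
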